### Randomisation

Participants are automatically randomised at the pre-intervention stage across the four experimental conditions, stratified by gender and category of medication intake, as specified here under:CategoryA (alcohol agonists and antagonists): Disulfiram, Naltrexone, Acamprosate and Gamma-hydroxybutyrate;Category B (psychoactive medication such as anxiolytic, antidepressant and neuroleptic medications);Category C (other medications).

Participants are randomly allocated to one of the conditions to which the fewest participants of their gender and medication category have been so far assigned.

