### Data analysis

Complete analyses will be conducted in agreement with Intention-To-Treat principle [26]. Missing data points will be handled with multiple imputation.

To answer to the main research question, a multiple logistic regression will be used to estimate how much the main and combined exposure to the two CBM modules affects the occurrence of lapse and/or relapse episodes at the three-month follow-up assessment.

The secondary research question, whether participants approach and attentional biases do change after the CBM intervention, is addressed via a 3×2×3 repeated-measures mixed ANOVA with the AAT and VPT scores as dependent variables, time (baseline, post-intervention and follow-up) as repeated measures within-subject factor, drink type (alcoholic and non-alcoholic) or attentional process (engagement and disengagement) as within-subject factor, and CBM condition (re-training or placebo) as between-subject factor. The same analysis applies to the continuous secondary outcome measures administered at each time point.

The third research question of the present study is framed within a ‘what works best for whom?’ approach [8] and explores the moderating and mediating roles of individual differences variables on the clinical outcome by means of a moderated mediation analysis [51]. More precisely, baseline strength of the cognitive biases and interference control capacity (Stroop task), as well as age, gender and previous detoxifications, are hypothesised to moderate the change in cognitive bias after the CBM intervention, which is further hypothesised to eventually mediate the change in the clinical outcome variable (see Eberl *et al*. [19]).

Finally, participants’ motivation to change (MAC2-A) at pre- and post-intervention will be compared via a paired t-test. Via a repeated-measures ANOVAs we will explore whether change in participants’ motivation to carry on with the training after the brief MS interviews affects attrition and training outcome.

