### Sample size

The sample size is limited to 120 recruited participants due to constraints in the ratio between the number of potential participants fully meeting the eligibility criteria and available to participate in the study, out of the total number of alcohol-dependent outpatients currently in charge in the public service at the time of recruitment (3:10). Therefore, a realistic estimate of 120 participants (n = 30 per experimental condition) was considered achievable for a phase II RCT study, and further supported by a minimum number of cases identification analysis.

An operational guideline to identify the minimum number of cases to include in the study has been suggested by the Peduzzi *et al*. [52]. For *k* independent variables and *p* as the smallest of the proportions of negative or positive cases in the population, then the minimum number of participants is 10*k/p. Based on three previous CBM studies with alcohol dependent clinical populations, the average proportions of occurrence or absence of relapse event(s) at follow-up are about 0.53 and 0.47 after an approach bias or control re-training, respectively [18,19]; and about 0.40 and 0.28 after an attentional bias or control re-training, respectively [17]. The proportions were computed out of the total number of enrolled participants.

By taking the minimum among the four proportion values and setting *k* = 2 (two independent variables: attentional bias CBM re-training or placebo and approach bias CBM re-training or placebo), the minimum number of cases to be included in the present study is 10*2/0.28 ≅ 71. According to this approach, the proposed sample size is more than adequate to answer to the primary research question of the present study and should also allow for high attrition rates. It is worth noting that Wiers *et al*. [18] and Eberl *et al*. [19] had a one-year follow-up period, whereas Schoenmakers *et al*. [17] had a three-month follow-up period. The different follow-up timing allows only a partial comparison of the above-mentioned proportions. If similar proportions at one-year of follow-up were also observed in Schoenmakers *et al*. [17] then the minimum number of cases would decrease to 10*2/0.47 ≅ 43.

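### Allocation is balanced on gender and medication category, but the primary logistic model as described omits both; if they predict relapse, the test is mildly conservative and loses a few points of power

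*Protocol article*

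**What the plan says.** Under Randomisation, allocation is "stratified by gender and category of medication intake". The medication factor has three levels, A, B and C. Each participant goes at random to one of the conditions to which the "fewest participants of their gender and medication category have been so far assigned", so balance is forced within each of the 2 × 3 = 6 cells.

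Under Data analysis, the main question is answered by a multiple logistic regression of how much "the main and combined exposure to the two CBM modules affects the occurrence of lapse and/or relapse episodes" at three months. No covariate is named. Under Sample size, the minimum-cases rule takes k = 2: "two independent variables: attentional bias CBM re-training or placebo and approach bias CBM re-training or placebo". The sensitivity power analysis in the same section uses a simple logistic regression for each module.

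Gender and medication have other roles. The aims section plans to explore their effect on the clinical outcomes, and Data analysis makes gender a hypothesised moderator.

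**The concern.** Balancing the conditions on factors that predict the outcome reduces the true sampling variability of the comparison between conditions. A logistic model without those factors computes its standard error as if allocation had been unrestricted. The standard error is then too large for the marginal effect, the true type I error falls below its nominal value, and some power is lost. The usual principle is to analyse by the factors used in the randomisation.

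The protocol gives some reason to think the factors matter. It chose to balance on them, and its Background reports that one earlier inpatient trial of approach-bias training showed lower relapse after controlling for gender. With the sample capped at 120 for practical reasons, precision that can be had through the analysis is worth having.

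**Working it through.** **Inputs from the protocol (Sample size):** N = 120, so 60 v 60 for each module's main effect; placebo relapse 0.60; detectable odds ratio 0.396; one-tailed test, critical z = −1.645; power 0.80; k = 2; p = 0.28 or 0.47.

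**Step 1. Reproduce the stated figure.**
- Active-arm rate: odds = 0.396 × 0.60/0.40 = 0.594, so p2 = 0.594/1.594 = 0.373.
- Wald form: the variance of the log odds ratio is 1/(60 × 0.60 × 0.40) + 1/(60 × 0.373 × 0.627) ≈ 0.141, so SE ≈ 0.375. Then |ln 0.396|/0.375 − 1.645 ≈ 0.926/0.375 − 1.645 ≈ 0.82, and power ≈ 0.795.
- Pooled two-proportion form: power 0.808.
- The detectable odds ratio at power 0.80 is 0.393 (Wald) or 0.400 (pooled). The stated 0.396 is reproduced. It is a marginal odds ratio, since it comes from a regression on one module alone.

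**Step 2. Simulate the allocation rule.** Each setting used 20,000 trials of 120, assigned at random among the least-filled conditions within the gender-by-medication cell and tested one-sided by Wald at −1.645. Marginal rates were held at 0.60 and 0.373, with no effect of the other module. The unadjusted model has the two modules. The adjusted model adds gender and two medication indicators.

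The article gives no figures for the following, so they are assumptions: 30% women; categories A/B/C at 40/35/25%; a stratum odds ratio of 1 to 3, applied to gender and to each medication step.

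| Stratum odds ratio | Type I error, unadjusted v adjusted | Power, unadjusted v adjusted | Conditional odds ratio matching marginal 0.396 |
|---|---|---|---|
| 1 | 0.056 v 0.058 | 0.806 v 0.816 | 0.396 |
| 1.5 | 0.048 v 0.051 | 0.812 v 0.829 | 0.384 |
| 2 | 0.043 v 0.051 | 0.813 v 0.842 | 0.362 |
| 3 | 0.038 v 0.055 | 0.828 v 0.877 | 0.321 |

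The power differences are 1.0, 1.7, 2.9 and 4.9 points. The simulation standard error near 0.05 is √(0.05 × 0.95/20,000) ≈ 0.0015. A repeat simulation at odds ratios 1, 2 and 3 agreed: type I error 0.052 v 0.055, 0.046 v 0.052 and 0.039 v 0.056; power 0.80 v 0.81, 0.82 v 0.85 and 0.82 v 0.87.

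At odds ratio 1 the strata carry no information, so the 1-point difference there is not a real gain. It goes with the slightly high Wald error of the larger model. The adjusted error of 0.051 to 0.058 accounts for part of the gap in the other rows too. Odds ratio 3 is a strong setting: over two medication steps and gender it means 3 × 3 × 3 = 27-fold odds between the extreme cells.

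**Step 3. Effect on the protocol's minimum-cases rule, 10k/p.**
- As printed: 10 × 2/0.28 = 71.4 and 10 × 2/0.47 = 42.6. Both match the article after rounding.
- With gender (1 term) and medication (2 terms), k = 5: 50/0.28 = 178.6, about 179, which exceeds 120; or 50/0.47 = 106.4, about 107, which does not.

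**The case against.** **The model may be fuller than the article shows.** Data analysis neither lists nor excludes covariates, and k = 2 is part of a sample-size heuristic that leaves out even the combined-exposure term. A fuller plan could add the strata. This stands as a caution. The point is about the model as described, and k = 2 and the exploratory role of gender and medication all point the same way.

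**The effect is conditional.** This stands. The article gives no prognostic strength for gender and nothing on whether medication category predicts relapse. Where the strata do not predict relapse, there is no conservatism and no real loss.

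**A sparse model is defensible by the protocol's own rule.** At p = 0.28, five predictors need more than 120 participants. This is a fair cost that has to be stated. It does not bar adjustment, because the same rule at the protocol's other value, 0.47, gives about 107.

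**Stronger readings that the documents do not support:**
- A reader might infer that power falls well below 0.80. Simulations with a two-sided test and 0.396 taken as a conditional odds ratio give unadjusted power of 65% and 54% at stratum odds ratios 2 and 3. The protocol plans a one-tailed test, and going two-sided alone brings power to about 0.69 to 0.71. Its 0.396 is marginal; treating it as conditional simulates a smaller effect, and adjusted power then falls as well, to 67% and 62%.
- A reader might infer that adjustment works by removing stratum variance from the error term. That is linear-model reasoning. In logistic regression, adjustment raises the standard error of the log odds ratio. The gain comes from a conditional odds ratio that lies further from 1.
- A reader might infer that unmedicated or multiply medicated participants cannot be allocated, because the printed list ends at "Category C (other medications". The list has no level for no medication and no rule for several drugs. But allocation is automatic, and coding rules of this kind are commonly left to the full protocol. On its own this is missing detail, not an error.

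**Conclusion.** The point holds as a modest, conditional recommendation. The allocation is balanced on two factors that the primary model, as described, leaves out. If those factors predict relapse, the unadjusted test errs on the conservative side: type I error of about 0.04 to 0.05 at a nominal 0.05, and about 1 to 5 points less power than the adjusted model over assumed stratum odds ratios of 1 to 3. Part of that gap is the adjusted model's slightly high Wald error.

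The omission does not inflate false positives, and the unadjusted test keeps about the stated 0.80 power in every setting examined. The exact figures depend on the assumed gender and medication mix.

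**What to change.** Prespecify gender and the medication stratum, as recorded by the allocation program, as covariates in the primary logistic model and in the secondary models. If they are to stay out, say so and give the reason.

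State two consequences alongside:
- The adjusted odds ratio is conditional on the strata and is not the quantity behind the stated 0.396. In the settings above, a marginal 0.396 corresponds to a conditional 0.384, 0.362 or 0.321. If the marginal effect is the target, report a standardised marginal effect from the adjusted model.
- Restate the 10k/p check with the real number of predictors. With k = 5 it gives about 179 at p = 0.28, above the fixed 120, or about 107 at p = 0.47, which leaves little room for attrition.

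As a secondary clarification, record how the allocation program codes participants who take no medication, or drugs from more than one category, so that the covariate matches the stratum actually used. If the program has a separate level for no medication, k becomes 6, and the rule gives 60/0.28 ≈ 214 or 60/0.47 ≈ 128.

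The cost is three or four model terms and a short statement. Recruitment is already under way, but nothing in the allocation needs to change; the choice only has to be fixed before the outcome data are unblinded.

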### Blinding

The trial has a double-blind design; hence, both participants and researchers do not know which experimental condition participants are assigned to. Participants create their personal research account at registration in the trial online platform and login to their personal account at each session. Participants are anonymised via the assignment of a user ID number. In order to reduce potential biases, participants complete online assessment measures, tasks and re-training interventions on their own at the computer, with the support of the researcher when requested. Furthermore, to keep participants blind to which intervention they receive they are required to respond to an irrelevant feature of the pictures in both CBM modules (orientation of the picture), instead of reacting to the content of the picture (alcoholic or non-alcoholic drinks) [28] (for a discussion about the difference between relevant- and irrelevant-feature tasks, see Wiers *et al*. and Field *et al*. [29,30]). Participants’ awareness about which experimental condition they are assigned to is assessed during the follow-up assessment.

### Intervention

Each CBM session starts with the brief MS interview (about 15 minutes), after which the motivation for training is briefly assessed, and proceeds with the two training modules (about 15 minutes each).

### Brief motivational support interview

According to the Trans-theoretical Model of Behaviour Change [31,32], which assumes that the changing process in health behaviour treatment is composed of six stages of readiness, from the pre-contemplation (avoidance and denial of a problem) to the maintenance (maintaining the successful changes into the daily life) stage, the participants of the present study are supposed to be in the fourth action stage of change, as assessed at baseline with the alcohol version of the motivation to treatment questionnaire (MAC-2A [33]). This stage is characterised by the pursuit of concrete decisions and behaviours aimed to tackle the addiction problem and to change the status quo, and by the establishment of an intentional commitment to the treatment process.

At the beginning of each training session, participants take part in a brief interview with a trained researcher (about 15 minutes), aimed at introducing the participant to the upcoming experimental session. The protocol of MS here devised has been partially inspired by the principles of the Motivational Interviewing approach [21], developed in the wake of the Trans-theoretical Model of Behaviour Change. Experimenters conducting the MS intervention are firstly trained with a professional in motivational interviewing, and later can practice the MS protocol during several role-plays with clinicians working in the addiction service. The interviewers regularly take part in supervision meetings with the same clinicians to discuss any issue related to the MS interviews.

The main objective of the MS during the action stage is to support the participants’ changes and progress reached so far in a constructive and open-minded way, by explicitly sustaining the efforts they are making to concretely face their addiction problems. In this context the efforts the participants are making include participation in the training sessions. The targeted MS then serves the purpose of preparing and introducing the participant to the upcoming experimental session, by rehearsing the objectives of the training, empowering the motivation to engage in the therapeutic process and sustaining the patient’s attention to the potential benefits of the CBM trainings. Namely, the strategies adopted in this phase are: reviewing progress, renewing motivation and redoing commitment [34].

In particular, each session of MS should cover the following topics:Review of the previous training session (except the first training session) and feedback to co-structure a positive framed feedback on the progress so far.Renewal and support of the motivation and compliance to the experimental intervention. According to the participant’s report of the previous session, the interview proceeds by shifting the attention to the motives that led the participants to start the change process, to support and/or empower them and remind them of the objectives of this training. The joint rehearsing of the motivations that brought the patient to undergo a treatment intervention (such as ‘I don’t want my loved ones to be ashamed of me’, ‘I don’t want my children to grow up with an alcohol addicted father/mother’, ‘I messed up my life because of the drinking’ and ‘I don’t want to feel like a loser anymore’) should work as a fuel for continuing the intervention (long-term goals) and prepare the ‘field’ for the engagement of top-down control processes.Empowerment of self-efficacy and affirmation of the current changing progresses. The training interventions are one of the concrete actions pursued by the participant to deal with the alcohol abuse. It is then important to explicitly acknowledge the progress (precision, constancy and commitment to the tasks) and to reinforce it (for example, by stressing that the practice effect can be a sign of individual efficacy in performing the tasks and increased control over the performance).Normalisation of any difficulty encountered in the training execution and reaffirmation of commitment (for example, by using the metaphor of gym training). Difficulty and boredom are common experiences that are intrinsically part of these kinds of interventions. In particular, the repetition of a certain behavioural pattern is a key component when the objective is to strengthen ability, or a muscle for example, or to increase the expertise and control in some life domains, such as a job activity. This strategy is functional to the reinforcement of the participant’s sense of autonomy and ability to pursue self-chosen goals and plans.Collaborative negotiation of the incoming session proximal goals. What are the expectations for the next session? What is the goal the participant would like to reach? For example, the proximal goal of increasing the response speed or reducing the number of errors sounds like a challenge for some participants and consequently stimulates their active involvement in the task.

Generally speaking, the interview is conducted with a specific, empathic and non-judgemental interviewing style and should be based on a concrete level of interaction, client-centred and focused on the introduction and practical discussion of the training sessions. The discussion of personal feelings and experiences related to the individual case study and relevant to the patient’s therapeutic path should be acknowledged but still re-addressed to the standard psychotherapeutic setting. According to the Trans-theoretical Model of Behaviour Change perspective, the change processes involved in the MS here devised deal with behavioural processes, namely, reinforcement of self-efficacy and managing strategies, stimuli control and relationship support, leaving the in-depth involvement of the experiential processes to the individual clinical setting.

Neither the participant nor the researcher knows to which experimental condition the participant has been assigned. If participants enquiry about their intervention condition the researchers will honestly disclose their own unawareness about participants’ allocation.

### Cognitive Bias Modification interventions

Each CBM training session consists of two modules: the attentional bias re-training and the approach bias re-training. Each task, both in the active and placebo version, consists of three blocks: a brief practice block, a mini-assessment block and a training block. The practice block presents neutral stimuli (grey geometrical pictures) to practice the task. The mini-assessment block serves the purpose of measuring the strength of the bias at the start of every session and tracking any change in the cognitive bias as a result of the CBM training.

In both tasks, each trial starts with a fixation cross in the middle of the screen for a duration randomly drawn from a *U*[500, 1,000] distribution. This setting was designed to make the task less boring, to keep participants’ attention focused and to avoid anticipatory responses. Whenever a wrong response is given, a red cross appears on the screen to allow for correction.

The two tasks were designed to be as similar as possible (same stimuli and number of trials) to avoid any confounding effect on participants’ performance. Their order of presentation is counterbalanced between subjects and fixed within subjects across all measurement time-points.

#### Attentional bias retraining

Attentional bias is assessed and trained through a modified version of the Visual Probe Task (VPT) [12,13,20], which is a computerised speeded reaction-time task in which participants are asked to respond to probes located in two different positions on the computer screen (irrelevant-feature implicit measure [30]). During the task, a picture of an alcoholic drink and a picture of a non-alcoholic drink are presented next to each other on the screen for 500 ms. After the stimuli presentation, a small arrow (8.3% of the width and height of the picture) pointing upwards or downwards is presented in either of two trial formats: in half of the trials it replaces one of the two pictures (after format), measuring speeded detection of alcohol-related stimuli (attention engagement), and in the other half it is positioned on top of one of the pictures (on-top format), measuring the relative difficulty to disengage from alcohol-related stimuli (attention disengagement). Participants are instructed to respond as fast as possible to the direction of the arrow by pressing the corresponding key on the keyboard (U and N) (for an example of a trial, see Figure 2). Response window is set to 4,000 ms; in cases of no response, the trial is restarted after repeating the task instructions.

**Figure 2 Fig2:**
[figure not shown]
**Example of trials in the attentional bias re-training (upper half) and in the approach bias re-training (bottom half).**

In the VPT assessment version and in the mini-assessment block during training, the arrow replaces the picture of alcoholics (alcohol trials) and non-alcoholics (non-alcohol trials) equally often. Attentional bias is computed by subtracting the median response time (RT) on alcohol trials from the median RT on non-alcohol trials, separately for after and on-top trial formats. In the training block, participants in the experimental condition are trained to direct their attention away from alcoholic drinks towards non-alcoholic drinks by exposing them only to non-alcohol trials, whereas participants in the placebo condition are presented with 50% alcohol and 50% non-alcohol trials (as in the VPT assessment version and in the mini-assessment blocks).

Stimuli are pairs of matched alcohol- and non-alcohol pictures, which are counterbalanced with a 2×2×2 design for assessment and placebo training (stimuli presented on the left and on the right, formats of arrow presentation and arrow location on the alcohol or non-alcohol picture), and with a 2×2 design for active training (stimuli presented on the left and on the right and formats of arrow presentation). The probe direction is set randomly upwards or downwards with the restriction that up and down appears equally often.

